## Abstract

**Background:**

The prevalence of asymptomatic bacteriuria (ASB) in pregnancy is 2-10% and is associated with both maternal and neonatal adverse outcomes as pyelonephritis and preterm delivery. Antibiotic treatment is reported to decrease these adverse outcomes although the existing evidence is of poor quality.

**Methods/Design:**

We plan a combined screen and treat study in women with a singleton pregnancy. We will screen women between 16 and 22 weeks of gestation for ASB using the urine dipslide technique. The dipslide is considered positive when colony concentration ≥10^5^ colony forming units (CFU)/mL of a single microorganism or two different colonies but one ≥10^5^ CFU/mL is found, or when Group B Streptococcus bacteriuria is found in any colony concentration. Women with a positive dipslide will be randomly allocated to receive nitrofurantoin or placebo 100 mg twice a day for 5 consecutive days (double blind). Primary outcomes of this trial are maternal pyelonephritis and/or preterm delivery before 34 weeks. Secondary outcomes are neonatal and maternal morbidity, neonatal weight, time to delivery, preterm delivery rate before 32 and 37 weeks, days of admission in neonatal intensive care unit, maternal admission days and costs.

**Discussion:**

This trial will provide evidence for the benefit and cost-effectiveness of dipslide screening for ASB among low risk women at 16–22 weeks of pregnancy and subsequent nitrofurantoin treatment.

**Trial registration:**

Dutch trial registry: NTR-3068

## Background

Asymptomatic bacteriuria (ASB) is the presence of significant bacteriuria without the symptoms of a urinary tract infection (UTI). ASB occurs in 2-10% of pregnant women [1]. ASB during pregnancy can lead to serious complications for both mother and child. The incidence of ASB is similar in both pregnant and non-pregnant women [2]. Pregnant women with ASB, however, develop pyelonephritis more often, probably due to the anatomic and physiologic changes that occur during pregnancy, which may facilitate bacterial growth and ascending of bacteria to the kidneys [3]. If left untreated, 20% to 40% of pregnant women with ASB will develop pyelonephritis [2,4,5].

Other possible adverse effects, such as preterm delivery and delivering a low birth weight infant are less well established. Preterm delivery is the main cause of neonatal mortality and morbidity worldwide. The causal mechanisms remain unknown. One of the hypotheses is that endotoxins released by bacteria cause uterine contractions leading to preterm delivery.

### Necessity of screening for ASB

Some national guidelines [1,6,7] recommend ASB screening and treatment in pregnancy. However, these guidelines are based on research conducted more than 30 year ago. Furthermore, our knowledge about methodology and the causing mechanisms of pyelonephritis has developed. Since the methods used in these early studies are inadequately described, interpretation of this evidence is difficult and the conclusions that can be drawn are limited.

Although many articles have been published on ASB in pregnancy, the role of ASB in perinatal outcomes is not clear [8]. Another problem is that most recent papers focus on the best treatment strategies instead of evaluating the actual need for a screen and treat program.

The widespread use of antibiotics as a consequence of the screening programs is reason for concern. The ORACLE Children Study II [9] showed increased functional impairment in children from mothers using antibiotics for the prevention of preterm labour in pregnancy. Other studies also showed an adverse effect of antibiotics on the offspring, such as increased antibiotic resistance in late-onset serious bacterial infections [10]^;^[11]. Considering these results, one should carefully balance the consequences of bacteriuria in pregnancy against the possible effects of antibiotics, before routinely treating all women with ASB.

### Antibiotics choice and duration

There is no consensus in the literature on either the duration of therapy or the choice of antibiotic. As a result practice is guided by national or local practices and resistance patterns[8]. A recent Cochrane review on the treatment duration for ASB underlines this lack of clear evidence on the best treatment[12].

The latest guidelines of the Infectious Disease Society of America (IDSA), published in 2005, recommend for the treatment of ASB a 3 to 7-day course for the treatment of ASB that includes sulphonamides, nitrofurantoin, nalidíxic acid, amoxicillin or trimethoprim [1].

E *coli* is the most common pathogen found in ASB [3] and treatment should be targeted to the most common pathogens. Nitrofurantoin has proven to be safe in pregnancy [13,14] with very low resistance levels in Netherlands [15]. Nitrofurantoin is first choice in the treatment of cystitis in pregnancy in the Netherlands [16,17].

The Dutch guidelines of the Dutch Society of Obstetrics and Gynaecology (NVOG ) and the Dutch General Practitioners Society (NHG) do not currently recommend routine screening and treatment of ASB in pregnancy[16,17] because convincing evidence is lacking. The Netherlands is one of the few countries which can still properly investigate this important question because a non treating policy of woman with ASB does not violate the guideline.

In view of the lack of good clinical evidence on the subject and the resulting practice variation, we think that an appropriately designed clinical trial evaluating the costs and effects of a screen and treat program is urgently needed. In a national cohort study women will be screened for ASB with the dipslide technique. Women with ASB will be randomised to either placebo or nitrofurantoin.

## Methods/design

### Outline

The study will be a prospective cohort screening study with a randomised clinical trial embedded. We will screen a large cohort of women with low risk singleton pregnancies at 16–22 weeks gestation with the dipslide technique. Women with a positive dipslide without symptoms of a UTI will be randomly allocated to receive either nitrofurantoin or placebo for 5 days. To mask women for their bacteriuria status a small sample of women without ASB will also be offered the possibility to participate in the study. Women without ASB will always receive placebo. Both women and researchers will be unaware of the bacteriuria status and treatment allocation. Because of the blinding of bacteriuria status, women with GBS bacteriuria will not receive intrapartum antibiotics in the absence of other risk factors.

The objective of the randomized trial is to evaluate whether nitrofurantoin treatment of women with ASB is effective in reducing the risk of preterm delivery and/or pyelonephritis (primary outcome) and adverse neonatal outcome (secondary outcome).

### Participants/eligibility criteria

The study is set in the Dutch Obstetric Consortium, a collaboration of obstetric practices in the Netherlands. A variety of clinics, including university hospitals, teaching hospitals, non-teaching hospitals, ultrasound centres and midwifery practices will participate in this trial. Women with a singleton pregnancy without symptoms of a urinary tract infection at 16–22 weeks of gestation can participate in the *ASB screening* study.

Women with a history of spontaneous preterm delivery before 34 weeks, signs of threatening preterm delivery, foetal congenital malformations, use of antibiotics at time of screening, known G6PD deficiency or allergy to nitrofurantoin or risk factors for complicated UTI (diabetes mellitus, immunosuppressive medication, functional or structural abnormalities of the urinary tract) are excluded from the screening study.

### Procedures, recruitment, randomisation and collection of baseline data

#### ASB screening trial

In the ASB *screening* trial, we will offer low risk women with a singleton pregnancy the possibility to be screened for ASB with the dipslide technique. At the 16^th^ week of gestation the timing of screening is considered optimal [4,18]. For logistic reasons we decided to do the screening at the same time the structural ultrasound scan for foetal abnormalities is performed in the Netherlands.

A single dipslide (Uricult®, Orion Diagnostica) consisting of two different media (green cysteine lactose electrolyte deficient medium and reddish MacConkey medium) will be used to diagnose ASB. Previous research showed that the dipslide is a promising alternative for the conventional culture, which is currently considered the gold standard[19,20]^;^[3]. The dipslide has 98.0% sensitivity and 99.6% specificity for detecting ASB in pregnancy [21]. Urinary culture is not feasible in the Dutch antenatal care system since 70% of Dutch women attend antenatal care at a midwifery practice. Hence, there is no direct access to a microbiology laboratory to perform the cultures.

The dipslide will be inoculated with midstream urine at a hospital, ultrasound centre or midwifery practice. Perineal cleansing prior to voiding is not necessary since it does not decrease bacterial contamination [22]. The dipslides will be sent by mail to the laboratory for infectious diseases in Groningen, the Netherlands the same day. Laboratory technicians will read the dipslide directly when incubated for 2 to 3 days at room temperature. If no colonies have been formed, the dipslide will be incubated for another 24 hours at 35^o^ Celsius.

Dipslides are considered positive when the colony concentration is ≥ 10^5^ CFU/mL of a single microorganism or when two different colonies are present but one has a concentration of ≥10^5^ CFU/mL. When Group B Streptococcus (GBS) is found also colony concentrations <10^5^ CFU/mL are considered positive because treatment may still be beneficial [23]. When more species are present the dipslide is considered contaminated.

All women participating in the ASB *screening* study will receive two questionnaires. The first questionnaire contains questions about ethnicity, marital status, length, weight, education, smoking, alcohol- and drug use, co morbidity, parity, inter-pregnancy interval and exclusion criteria. This questionnaire will be filled out at the moment of screening. The second questionnaire will be sent to the participants 6 weeks after their due date. It contains questions about UTIs, use of antibiotics and hospital admissions during this pregnancy, pregnancy complications and pregnancy outcomes. Furthermore we will ask all women in the screening study for informed consent to collect data on their pregnancy outcomes.

#### ASB treatment trial

Women eligible for the ASB *treatment trial* will be identified by the laboratory personnel participating in this study. A research midwife or -nurse will contact these women for participation in the treatment trial.

Before entering the study, women will be informed about the aims, methods, reasonably anticipated benefits and potential hazards of the study. Participation is voluntary and withdrawal of consent to participate is possible at any time during the study. After giving sufficient information, written informed consent will be asked for. Women eligible for the ASB *treatment trial* who do not give informed consent, will be registered. Nitrofurantoin will not be offered to these women.

After participant data have been entered in a web based database, computerized randomisation will take place. The women with ASB will be randomised 1:1 for nitrofurantoin and placebo. Women without ASB (used for blinding of bacteriuria status) will always receive placebo.

### Intervention

Each study participant will be given a jar labelled “ASB *treat* study” which contain either 100 mg capsules of nitrofurantoin (Nitrofurantoin MC, TioFarma, the Netherlands) or identical-appearing capsules of placebo (TioFarma, the Netherlands).

The oral study medication will be self-administered twice a day for 5 consecutive days. The label codes indicating nitrofurantoin or placebo are blinded for the participants and researchers. The deblinding list is present in the central pharmacy. For emergency cases, a closed envelope with the label codes is also available at the study centre. The data will be disclosed to the researchers in case of emergencies and otherwise after collection and analysis of the primary outcomes. Researchers involved in the follow up program of the offspring of women participating in this study will remain blinded for a longer period. For purpose of the interim analysis the label codes will become available to the epidemiologist involved in the study as A and B.

All participants who receive study medication -i.e. the screen positives as well as the random subsample of screen negatives-, will have follow up dipslides done 1 week after the end of treatment. Participants with a persistent positive culture and a subsample of participants with a negative culture will receive again (blinded) study medication. The participants who received nitrofurantoin will again receive nitrofurantoin, placebo participants will again receive placebo. One week after this second intervention, once again a dipslide is performed.

### Outcome measures

The primary outcomes for the screen and treat study are the development of pyelonephritis and delivery before 34 weeks. Pyelonephritis is defined as an episode of fever (≥38.0°C), symptoms (nausea, vomiting, chills, costo-vertebral tenderness) and a positive urine culture. The primary outcome measure will be recorded 6 weeks after the expected due date.

Secondary outcome is an adverse neonatal outcome (death or severe morbidity). The composite morbidity rate contains the following variables: severe respiratory distress syndrome (RDS), bronchopulmonary dysplasia (BPD), periventricular leucomalacia > grade 1, intracerebral haemorrhage > grade II, necrotizing enterocolitis (NEC) > stage 1, proven sepsis (including GBS sepsis) and death before discharge from the nursery.

Other outcome parameters are: neonatal weight, time to delivery, preterm birth rate before 32 and 37 weeks, days of admission in neonatal intensive care unit, maternal morbidity (including UTI), chorioamnionitis, maternal admission days for (threatened) preterm labour and/or pyelonephritis and costs.

Furthermore, we will look at growth, physical condition and neurodevelopmental outcome of the child at 24 months (corrected) age.

Apart from clinical outcome, the cost-effectiveness of screening for ASB (as done in ASB *screening*), and subsequent treatment in cases of ASB (as done in ASB *treatment trial*), will be assessed.

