### Data analysis

The results of the screen cohort will allow us to describe the incidence of ASB in the Netherlands as well as to explore risk factors for developing ASB or pyelonephritis.

The results of the randomised clinical trial will be analyzed according to the intention to treat principle. The effectiveness of nitrofurantoin versus placebo will be assessed by calculating relative risks and 95% confidence intervals. The number of primary- and secondary outcomes will be compared between the ASB positive and ASB negative (ASB screen study) and treatment and control (ASB treat study) groups.

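### The adverse neonatal outcome has no place for fetal death after randomisation, so an excess of losses in one arm would not show in it

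*Protocol article*

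**What the plan says.** The Outcome measures section names adverse neonatal outcome, glossed as death or severe morbidity, as the secondary outcome. The Outline gives it the same role in the trial objective. The content is then itemised: "The composite morbidity rate contains the following variables", followed by six severe neonatal morbidities, the last of them sepsis, and then death: "proven sepsis (including GBS sepsis) and death before discharge from the nursery". No other death component is given.

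The remaining clinical outcomes begin "Other outcome parameters are: neonatal weight, time to delivery, preterm birth rate before 32 and 37 weeks" and go on to intensive care days, maternal morbidity, chorioamnionitis, maternal admission days and costs. Stillbirth, late miscarriage and fetal death are named nowhere among the outcomes, in that section or in the Abstract.

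Entry is early. Participants/eligibility criteria admits to screening "Women with a singleton pregnancy without symptoms of a urinary tract infection at 16–22 weeks of gestation", and randomisation follows the dipslide result and consent. For the analysis, the Data analysis section says "The results of the randomised clinical trial will be analyzed according to the intention to treat principle", with effectiveness "assessed by calculating relative risks and 95% confidence intervals". It gives no rule for a pregnancy that ends without a liveborn child.

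**The concern.** Randomisation takes place around mid-pregnancy, so follow-up covers the period in which late miscarriage, previable delivery and stillbirth occur. A fetus that dies before birth never reaches a nursery and cannot acquire any of the listed morbidities. The article's Background offers bacterial endotoxins provoking contractions as one possible route to preterm delivery, so very early loss could lie on the pathway under study.

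Fetal death is thus a competing event, worse than any listed component, that removes the infant from risk of all of them. If one arm had more losses, this outcome would be silent about it, and its relative risk could point the other way from the total of deaths and severe morbidity.

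**Working it through.** **The plan's own figure.** The article gives no rate or sample size for this composite, only for the primary outcome: 10% vs 25%, two-sided alpha 0.05, a stated beta of 0.8 (read as power 0.80), 110 per arm. The two-proportion formula is n = [1.96·√(2·p̄·(1−p̄)) + 0.8416·√(p1(1−p1) + p2(1−p2))]² / (p1−p2)².

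- With p̄ = 0.175: [1.96·√0.28875 + 0.8416·√0.2775]² / 0.0225 = 99.5, so 100 per arm.
- With continuity correction: (99.5/4)·[1 + √(1 + 4/(99.5·0.15))]² = 112.5, so 113 per arm, within 3% of 110.

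The stated 110 is therefore reproduced closely enough to use as the arm size below. It does not bear on how the composite is defined.

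**What happens to a fetal death.** Two readings are open under the text as written:

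1. Every randomised woman is in the denominator. The fetal death meets no component and scores zero.
2. Only liveborn infants are in the denominator. The fetal death disappears, and the comparison is conditioned on survival to birth, a post-randomisation event.

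**Size.** Assumed inputs, none of them in the article: composite rate m among liveborn infants equal in both arms (3%, 5% or 10%), and fetal deaths f1 and f2 in two arms of 110.

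- Scored event-free: RR = m(110−f1) / m(110−f2) = (110−f1)/(110−f2)
- Dropped: RR = m/m = 1.00
- Counted as events: RR = [m(110−f1)+f1] / [m(110−f2)+f2]

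| Fetal deaths | m | Event-free | Dropped | Counted |
|---|---|---|---|---|
| 4 vs 1 | 3% | 106/109 = 0.97 | 1.00 | (3.18+4)/(3.27+1) = 1.68 |
| 4 vs 1 | 5% | 0.97 | 1.00 | (5.30+4)/(5.45+1) = 1.44 |
| 4 vs 1 | 10% | 0.97 | 1.00 | (10.6+4)/(10.9+1) = 1.23 |
| 2 vs 1 | 3% | 108/109 = 0.99 | 1.00 | (3.24+2)/(3.27+1) = 1.23 |
| 2 vs 1 | 5% | 0.99 | 1.00 | (5.40+2)/(5.45+1) = 1.15 |
| 2 vs 1 | 10% | 0.99 | 1.00 | (10.8+2)/(10.9+1) = 1.08 |

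These are expected counts used to show direction and size. They are not tests.

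**What the other outcomes pick up.**

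- Delivered before 34 weeks: on plain wording this is a primary event, because the definition does not require a live birth. A stillbirth then carries the same weight as a healthy birth at 33 weeks.
- Delivered at 34–36 weeks, no pyelonephritis: outside the primary outcome and the composite. It is counted in the preterm rate before 37 weeks, which does not record vital status.
- Delivered at or after 37 weeks, no pyelonephritis: outside the primary outcome, the composite and every preterm threshold. Time to delivery would register the date only.

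**The case against.** A reader might infer that the definition makes an arm with more stillbirths look materially better. The figures do not support that: the relative risk moves only to 0.97 when fetal deaths are scored event-free, and not at all when they are dropped. Nor does the article state that a fetal death is scored as no event. That is the literal result of the component list combined with an all-randomised denominator, and the other reading remains open.

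The strongest counter-argument is the primary outcome. Losses delivered before 34 weeks fall under it as worded, so it would be wrong to say that fetal loss escapes the trial's endpoints altogether. This stands and narrows the concern. It does not remove it, because the primary outcome does not separate dead from living infants and does not reach deliveries from 34 weeks on.

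One could also call this detail that a condensed article leaves to the full protocol. That is fair for the bare denominator rule. It does not cover the component list, which the article sets out in full, tying death to nursery discharge. The gloss of death or severe morbidity does not rescue it, since it explains a neonatal outcome. Reporting of serious adverse events to the monitoring committee is a safeguard, but not a comparison of outcomes between arms.

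Finally, calling this the leading secondary outcome needs care. Outcome measures and the Outline single it out, whereas the Abstract lists several secondary outcomes without ranking them.

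**Conclusion.** The concern holds as a defect of definition that can hide harm. Followed as written, the composite gives a fetal death after randomisation no place, and one of the two ways of handling it conflicts with the intention-to-treat statement.

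The false benefit is small: 0.97 or 1.00 for an assumed 4 vs 1 fetal deaths. The hidden excess is not: 1.23 to 1.68 when those deaths are counted, and 1.08 to 1.23 for 2 vs 1. These figures rest on assumed numbers of losses, assumed composite rates of 3–10% and equal rates among liveborn infants in both arms. The article supplies none of these. The gap in the definition does not depend on them.

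**What to change.** In Outcome measures:

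- Redefine the death component as fetal death at any time after randomisation, or neonatal death before discharge, and rename the outcome to match.
- Set the denominator as all randomised women with bacteriuria, one outcome per pregnancy. The screen-negative women given placebo for blinding stay outside this comparison.
- Report fetal death separately by arm, so that the composite does not mask it.
- State that any delivery or pregnancy loss after randomisation and before 34 weeks counts in the primary outcome.

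The cost is a few sentences. Pregnancy outcomes are already to be collected, by consent and by the questionnaire sent after the due date. The sample size rests on the primary outcome and is unchanged. The downside is that some losses unrelated to infection will be included. Randomisation should spread these evenly, so they dilute the effect slightly but do not favour either arm.

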### Follow up of women and infants

We plan follow-up of infants at the corrected age of 24 months with the Ages & Stages Questionnaires (ASQ) and the Child Behavioural Checklist (CBCL). The checklists will be sent to the parents of the child. In case the parents do not return the questionnaire, a reminder will be sent. We will also ask them to report length, weight medical history and medical consumption of the child.

### Data analysis

The results of the screen cohort will allow us to describe the incidence of ASB in the Netherlands as well as to explore risk factors for developing ASB or pyelonephritis.

The results of the randomised clinical trial will be analyzed according to the intention to treat principle. The effectiveness of nitrofurantoin versus placebo will be assessed by calculating relative risks and 95% confidence intervals. The number of primary- and secondary outcomes will be compared between the ASB positive and ASB negative (ASB screen study) and treatment and control (ASB treat study) groups.

